### Recruitment of patients

Patients will be screened by a member of the research team from those admitted to the emergency department of both clinical centers involved in the study. Patients diagnosed with AMI will be invited to participate in the study.

Informed consent will be obtained from suitable patients or their representative by one of the investigators or a delegated subinvestigator at each site. A member of the research team will answer all questions regarding the study and risks of the protocol procedure before the patient signs an informed-consent form.

### Sample size

Taking into account that until 50% infarct size is due to reperfusion damage, a minimal efficacy of the intervention is considered to reach a relative improvement up to 25% infarct size. Similar studies applying the same method have provided the accuracy of measurements as variance value. The sample size was calculated from the following formula [76]:

$$n=2{\left(\mathrm{ZS}+\mathrm{ZP}\right)}^{2}x\;S^{2}/{\left(\mathrm{MA}–\mathrm{MB}\right)}^{2}$$

Where *n* is the sample size for each group, “ZS” corresponds to the level of significance (5%), “ZP” represents the potency (80%), “MA” is the mean of supplemented group,MB, the mean of the placebo group (control), and S is the variance of CMR determination for assessment for IS. A 10% patient loss was considered for the purposes of this calculation. This calculation rendered a sample size of 66 patients for each branch (placebo and supplemented). This sample size is suitable to be covered by the population of patients being treated for PCA in the Cardiovascular Department, University of Chile Clinical Hospital, and Cardiovascular Center, San Borja Arriarán Clinical Hospital, during the estimated period (3 years).

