**Methods/Design:**

This is a randomized, 1:1, double-blind, placebo-controlled clinical trial.

The study takes place at two centers in Chile: University of Chile Clinical Hospital and San Borja Arriarán Clinical Hospital.

The subjects will be 134 adults with acute myocardial infarction with indication for percutaneous coronary angioplasty.

This intervention is being performed as a pilot study, involving high-dose vitamin C infusion plus oral administration of vitamin E (Vitamin-treatment group) or placebo (Control group) during the angioplasty procedure. Afterward, the Vitamin-treatment group receives oral doses of vitamins C and E, and the Control group receives placebo for 84 days after coronary angioplasty.

Primary outcome is infarct size, assessed by cardiac magnetic resonance (CMR), measured 6 and 84 days after coronary angioplasty.

Secondary outcomes are ejection fraction, measured 6 and 84 days after coronary angioplasty with CMR, and biomarkers for oxidative stress, antioxidant status, heart damage, and inflammation, which will be measured at baseline, at the onset of reperfusion, 6 to 8 hours after revascularization, and at hospital discharge.

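### The sample size formula defines S as the variance of the CMR measurement and squares it, where the between-patient SD of infarct size is needed, and the total is 132 in one place and 134 in another

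*Protocol article*

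**What the plan says.** The Sample size section of the protocol article sets n per group equal to 2(ZS + ZP)² × S² / (MA − MB)², with 5% significance, 80% power and an allowance of 10% for patient loss. MA and MB are the means of the supplemented and placebo groups.

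- **Effect:** "a minimal efficacy of the intervention is considered to reach a relative improvement up to 25% infarct size".
- **Definition of S:** "S is the variance of CMR determination for assessment for IS".
- **Source of S:** "Similar studies applying the same method have provided the accuracy of measurements as variance value".
- **Result:** "This calculation rendered a sample size of 66 patients for each branch (placebo and supplemented"; that is 132 in total.

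The Abstract, under Methods/Design, gives another total: "The subjects will be 134 adults with acute myocardial infarction". The Statistical analyses section plans an unpaired Student t test for continuous variables.

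**The concern.** Two things are wrong in how S is described.

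1. **Scale.** The formula squares S, so S has to be a standard deviation. If S is already a variance, the numerator holds a squared variance.
2. **Quantity.** Both sentences about S refer to how precisely CMR determines infarct size. An unpaired comparison of group means depends on how much infarct size varies from patient to patient. The Statistical analyses section itself names sources of that variation (myocardium at risk, infarct location, time to reperfusion) and says that stratification was discarded. Measurement error contains none of them.

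Infarct size is the primary outcome and the 80% power claim is made for it. If a measurement-error figure really was entered, the relevant SD would be larger and the power below 80%. A null result could then be read as evidence of no effect when the trial had limited ability to find one. The two totals are a smaller matter, but they leave two recruitment targets on record.

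**Working it through.** **Inputs from the protocol article:** significance 5%, power 80%, relative reduction 25%, loss 10%, allocation 1:1, result 66 per arm, Abstract total 134.

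**Assumptions:** a two-sided test (sidedness is not stated); S read as an SD; about 60 evaluable patients per arm (66 × 0.90 = 59.4); and SD expressed as a share of the control mean, because the article gives no value for it.

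**Step 1: can 66 be reproduced?** Not forwards, since the article gives no values for S, MA or MB. It can only be solved backwards.

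**Step 2: back-solve.**
- 2(1.960 + 0.8416)² = 15.70, so n = 15.70 × (SD/difference)².
- With n = 60: SD/difference = √(60/15.70) = 1.955.
- The difference is 25% of the control mean, so SD = 1.955 × 0.25 = 0.489, or about 49% of the control mean.

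How this moves with the assumptions:

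| Evaluable per arm | Test | Implied SD, % of control mean |
|---|---|---|
| 59.4 | two-sided | 48.6 |
| 60 | two-sided | 48.9 |
| 66 | two-sided | 51.3 |
| 60 | one-sided | 55.1 |

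**Step 3: power over an assumed range of SDs.** Two-sample t test, two-sided 5%, 60 evaluable per arm, standardised effect = 0.25 / (SD/mean). The last column is 15.70 × (SD/mean)² / 0.25², rounded up.

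| SD, % of control mean (assumed) | Power, % | Evaluable per arm for 80% by the plan's formula |
|---|---|---|
| 40 | 92 | 41 |
| 45 | 86 | 51 |
| 50 | 78 | 63 |
| 60 | 62 | 91 |
| 70 | 49 | 124 |

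The formula is a normal approximation. At an SD of 49% the t test gives 79% power where the formula gives 80%, so the break-even is "about" 49%.

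**Step 4: S taken literally as a variance.** As an illustration, assume a control mean of 20, so a difference of 5, and the back-solved SD of 1.955 × 5 = 9.775. The variance is 95.56. Entering that as S gives 15.70 × 95.56² / 5², about 5,734 per arm (unrounded inputs). The definition cannot be applied as written.

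**Step 5: 132 against 134.** 2 × 66 = 132. One possible route to both totals is a base of 60 per arm: 60 × 1.10 = 66 (132), and 60 / 0.90 = 66.7, rounded up to 67 (134). But 59 / 0.90 = 65.6 also rounds up to 66. The article states neither the base nor the inflation method, so the origin of the gap is conjecture.

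**The case against.** The strongest reply is that "variance" is a slip of terminology. The printed formula is standard if S is an SD, and Step 4 shows that on its illustrative inputs a literal variance gives nothing like 66, so an SD was very probably entered. The back-solved SD of about 49% of the control mean also looks large for pure measurement error in a method that the Background calls the gold standard. It is compatible with real patient-to-patient spread, loosely described. This stands: it prevents any inference that the arithmetic behind 66 was wrong. It does not repair the text, which names the wrong quantity in two sentences.

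Three stronger readings are tempting and are not supported.

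- **That the trial is underpowered.** No document gives the SD. Below about 49% of the mean, power exceeds 80% under the stated assumptions; above it, power falls short.
- **That leaving out values for MA, MB and S is an error.** A journal article condenses a fuller protocol that is not shown, so this only means that 66 cannot be checked from the article.
- **That 134 is the right total and 132 reflects a faulty dropout inflation.** That rests on a guessed base of 60. The gap of two patients hardly affects power: at an SD of 48.9% of the mean, the t test has 78.9% power with 59.4 evaluable per arm and 79.3% with 60.

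The trial is also labelled a pilot, which softens the consequence. It does not remove it, since the article still claims 80% power.

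**Conclusion.** The point holds in a limited form. As described, S is the wrong quantity on the wrong scale, so the stated basis for 80% power is wrong. Whether the number actually entered was wrong cannot be told from the article, and 66 per arm is not shown to be too small. Reading S as an SD, with a two-sided 5% test, about 60 evaluable per arm and a 25% relative reduction, the power claim is sound only if the between-patient SD is at most about 49% of the control mean. The sidedness and the 60 are assumptions, as are the SDs in the table. The 132/134 contradiction is certain on the face of the text but small, and does not by itself undermine the power.

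**What to change.** - Define S as the between-patient SD of infarct size. Confirm from the source studies that the value used was that quantity, then rerun the formula with it.
- State one total throughout, 132 or 134, with the loss allowance applied by dividing by 0.90.
- If the sourced SD exceeds about 49% of the control mean, keep the sample size and restate the power or the detectable reduction. With 60 evaluable per arm, the reduction detectable with 80% power is about 26% at an SD of 50% of the mean, 31% at 60% and 36% at 70% (t test).

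The cost is a recalculation and a few sentences. It needs no outcome data, and the Trial status section reports recruitment still in progress with 43 patients enrolled. The downside is that the stated power may become less favourable.

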### Randomization and followup

Patients will be randomly allocated to one of the two groups. The allocation sequence will be centrally generated, stored, and assigned by using online randomization software (http://www.randomization.com) in random permuted blocks, each consisting of a box containing six treatment kits allocated in a placebo-to-vitamin treatment, 1:1 ratio for each participating center.

Random allocation is generated by intervention of the technician responsible for the treatment assignment to recruited patients, according to the sequence already established through the randomization method indicated previously. The reasons for losses and exclusions after randomization will be provided.

Neither participants, nor care providers, nor the investigators are aware of the treatment assignments. Adverse events, unintended effects and technical problems will be recorded.

### Interventions

All patients will be asked to sign the informed consent before beginning the protocol. For those patients allocated to receive vitamin treatment, the intervention will be started as soon as the patient has signed the informed consent. The protocol will be started by administering an unique oral dose of vitamin E as α-tocopherol (800 IU) and an intravenous infusion of vitamin C as sodium ascorbate (320 m*M*) infused at a 10-ml/min flow rate during the initial hour and at 3 ml/min rate during the following 2 hours. Percutaneous coronary angioplasty will be performed about 30 minutes after initiating the vitamin C infusion. Oral doses of vitamin E (400 IU/day) and vitamin C (500 mg/12 hours) will be taken by the patients for 84 days after PCA.

For those patients allocated to receive placebo treatment, the 800-IU oral dose of vitamin E will be replaced for two vegetable oil capsules (400 mg each). The intravenous infusion of vitamin C will be replaced by an equal sodium chloride solution volume having the same osmolality as the vitamin C infusion administered to supplemented patients. The 400-IU oral doses of vitamin E will be replaced by vegetable oil (400 mg), and oral doses of vitamin C will be replaced with inert starch microgranules (500 mg). The pharmaceutical forms of vitamin C and E are indistinguishable from their respective placebos.

After the initial evaluation, patients will go to the catheterization laboratory. According to the standard protocol in AMI, an angiography will be performed to identify the infarct-related artery. The location and extent of AMI (number of arteries involved), percentage of stenosis, TIMI flow, type of stent, and so on, will be recorded. Immediately before coronary arteriography to confirm total occlusion of one coronary artery, a basal blood sample will be drawn from the antecubital vein. Three more blood samples will be obtained: immediately after successful reperfusion, at 6 to 8 hours after finishing the revascularization process and before hospital discharge.

Infarct size, the primary endpoint of the study, will be measured with cardiac magnetic resonance (CMR) at 6 and 84 days (12 weeks) after PCA. Both determination and data obtained by these procedures will be evaluated by two independent individuals with the purpose of applying the concordance kappa index. Adherence to oral intake of vitamins C and E or placebo will be evaluated by telephonic contact effectuated weekly by the nurse responsible for the trial patient´s care.

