### Primary and secondary outcomes

Primary outcome will be infarct size, which will be measured with CMR at 6 and 84 days (12 weeks) after PCA. Both determination and data obtained by these procedures will be evaluated by two blinded independent individuals with the purpose of applying the concordance kappa index.

As our primary outcome is fully dependent on a high-quality blood-flow restoration to the ischemic myocardium region, we established as our criteria for successful reperfusion only patients who have a starting TIMI flow of 0 in the PCA and finish the procedure with TIMI flow 3, according to the most rigorous literature standards [77-79]. Secondary outcomes will be myocardial-damage biomarkers, oxidative stress- and inflammation-related biomarkers, and ejection fraction.

1. Ejection fraction: will be measured with cardiac magnetic resonance (CMR) at 6 and 84 days (12 weeks) after PCA. Both determination and data obtained by these procedures will be evaluated by two blinded independent individuals with the purpose of applying the concordance kappa index.

2. Oxidative stress-related biomarkers:

Plasma protein carbonylation

Antioxidant capacity of plasma: Ferric reducing ability of plasma (FRAP)

Plasma concentration of vitamins C and E

Thiol index: GSH/GSSG ratio in erythrocytes

Lipid peroxidation: F2-isoprostane and malondialdehyde levels in plasma and erythrocytes, respectively, will be measured.

3. Inflammation biomarkers:

High-sensitivity C-reactive protein

Leukocyte count by standard method

4. Myocardial-damage biomarkers:

Troponin, CK, and CK-MB will be measured in plasma with standard methods

Oxidative stress- and inflammation-related biomarkers and myocardial-damage biomarkers will be assessed through antecubital venous blood extraction, at the moment of enrollment (30 to 60 minutes before PCA), immediately after successful reperfusion, at 6 to 8 hours after finishing the revascularization process and before discharge, as previously described. The samples will be collected in chilled vacutainers containing disodium EDTA (final concentration, 4 m*M*) and centrifuged at 3,000 *g* for 10 minutes to separate the plasma from figurate elements. Erythrocytes will be subjected to hypotonic hemolysis by dilution with distilled water. Plasma and red blood cell lysates will be stored at -80°C until performing the biochemical analyses.

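### The protocol gives two conflicting times for the basal blood sample, and neither secures a draw before study treatment starts

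*Protocol article*

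**What the plan says.** The Interventions section of the protocol article fixes this sequence:

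- For the vitamin arm, "the intervention will be started as soon as the patient has signed the informed consent". The first step is a single oral dose of vitamin E together with the vitamin C infusion at 320 mM, which is to be "infused at a 10-ml/min flow rate during the initial hour and at 3 ml/min rate during the following 2 hours".
- On when the procedure takes place, the section states: "Percutaneous coronary angioplasty will be performed about 30 minutes after initiating the vitamin C infusion".
- The patient then goes to the catheterization laboratory, where "an angiography will be performed to identify the infarct-related artery".
- On the first sample, it states: "Immediately before coronary arteriography to confirm total occlusion of one coronary artery, a basal blood sample will be drawn from the antecubital vein".

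The Primary and secondary outcomes section times the same first sample differently. It lists the draws as "at the moment of enrollment (30 to 60 minutes before PCA), immediately after successful reperfusion", followed by the two later draws, and refers back to the earlier description as if the two matched. It applies this schedule to all blood markers: "Oxidative stress- and inflammation-related biomarkers and myocardial-damage biomarkers will be assessed through antecubital venous blood extraction".

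Objectives iii and iv ask for oxidative-damage and antioxidant levels at baseline as well as at the later times. The Statistical analyses section includes a repeated-measures analysis of variance. Neither account of the sample says that it comes before the first study treatment.

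**The concern.** A baseline is useful only if treatment cannot have altered it. Read as a sequence, the Interventions section doses first and samples afterwards. The other section appears to sample first. Sites following different sections would draw the sample at different points relative to the infusion.

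The markers most exposed are those that the infusion acts on directly. Plasma vitamin C is a listed outcome and is the infused substance. FRAP measures the reducing capacity of plasma, to which ascorbate, itself a reductant, very probably contributes. The glutathione ratio and the lipid peroxidation markers might also move. An on-treatment first value in the vitamin arm alone could look like a chance imbalance between the arms. It would also hide part of the treatment effect in any analysis that measures change from that value.

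**Working it through.** The plan states no calculated figure on this point, so there is none to reproduce. The check is a timeline.

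**Inputs from the protocol article**
- Infusion start to PCA: about 30 min (Interventions).
- Infusion: 320 mM = 0.320 mmol/ml, 10 ml/min for 60 min, then 3 ml/min for 120 min (Interventions).
- Draw A: immediately before arteriography (Interventions).
- Draw B: 30 to 60 min before PCA (Primary and secondary outcomes).

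**Assumption**
- The gap *g* from arteriography to PCA is not given; only the order is. I let it run from 0 to 30 min.

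**Step 1: total infusion.** 10 × 60 + 3 × 120 = 960 ml; 960 × 0.320 = 307.2 mmol.

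**Step 2: draw A.** Set PCA at time 0, so the infusion starts at −30 min and the draw falls at −*g*. Infusion minutes = 30 − *g*; volume = 10 × (30 − *g*) ml; ascorbate = volume × 0.320 mmol.

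| Assumed gap (min) | Infusion before draw (min) | Volume (ml) | Ascorbate (mmol) | Share of 960 ml |
|---|---|---|---|---|
| 0 | 30 | 300 | 96 | 31% |
| 10 | 20 | 200 | 64 | 21% |
| 20 | 10 | 100 | 32 | 10% |
| 30 | 0 | 0 | 0 | 0% |

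**Step 3: draw B.** A draw at −60 to −30 min, with the infusion starting at −30 min, falls 30 to 0 min before the infusion. At the 0-minute end, draw and infusion start coincide and no order is fixed.

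**Step 4: can both hold?** Draws A and B coincide only if *g* is at least 30 min. Nothing in the article says that it is.

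**Step 5: rough size in plasma.** The article gives no plasma level for this stage of the infusion. As an order of magnitude only, assume full dilution in 30 to 50 litres of body water and no excretion. Gaps of 20 down to 0 min (32 to 96 mmol) then give 32/50 = 0.64 mM to 96/30 = 3.2 mM. The Background puts the oral steady state at about 80 µM (0.08 mM), so this is 0.64/0.08 = 8 to 3.2/0.08 = 40 times that level.

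**Step 6: effect on an analysis of change.** Let *E* be the treatment effect at a later sample and *d* the effect already present in the vitamin-arm first sample. The between-arm difference in change is then *E* − *d*. The between-arm difference at the later sample itself remains *E*.

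**The case against.** The strongest reply is that the article calls this sample baseline in the abstract and the objectives, and that the outcomes section ties it to enrolment and cross-refers to the earlier text. On that view the authors have one pre-treatment schedule in mind, and the Interventions sentence is loosely worded. If the enrolment timing governs, the sample precedes or coincides with the start of the infusion and no contamination arises. This stands as far as it goes: contamination is conditional, not established. It does not remove the conflict, because the Interventions sequence, followed as written, can produce an on-treatment sample.

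Three further limits also stand.

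- A reader might infer that the sample is taken after 20 to 30 minutes of infusion. That needs a gap of 0 to 10 minutes, which the article does not state. Its figures support only 0 to 30 minutes.
- A reader might infer that every biomarker is compromised. One sample serves all the markers, but nothing in the article suggests that troponin, CK, CK-MB, C-reactive protein or leukocyte count would shift materially before reperfusion. The placebo arm receives an equal infusion volume, so dilution is balanced.
- A reader might extend the problem to objective v or to a baseline-adjusted biomarker analysis. Objective v correlates biomarkers with infarct size and ejection fraction and names no baseline. The article specifies no change-from-baseline analysis of biomarkers. The repeated-measures analysis would, however, include the first sample.

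**Conclusion.** The point holds as an internal contradiction with a conditional consequence. The two sections time one sample differently, and neither requires it to precede the first study treatment. If the Interventions timing governs, the vitamin-arm sample follows 0 to 30 minutes of infusion, or 0 to 96 mmol ascorbate. This rests on the stated interval of about 30 minutes and on an assumed arteriography-to-PCA gap of 0 to 30 minutes. For any gap under 30 minutes, plasma vitamin C is a treatment value, FRAP very probably is, and other redox markers may be. That affects the baseline levels in objectives iii and iv and any repeated-measures or change analysis.

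It would be wrong to infer a threat to the main result. CMR infarct size at days 6 and 84 does not use this sample, and between-arm comparisons at reperfusion, at 6 to 8 hours and at discharge remain valid. This should be fixed, but it concerns secondary outcomes of a pilot trial.

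**What to change.** Reconcile the two sections to one sampling rule: draw the baseline sample after consent and before both the first oral capsule and the start of the infusion. Record the clock times of the draw and of infusion start. This changes only when the blood is drawn, not the treatment.

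The Trial status section reports 43 patients enrolled, against 134 planned in the abstract. For these patients:

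- Check the draw and infusion-start times in both arms and flag samples drawn after the infusion began.
- In the main biomarker analysis, do not treat flagged values as pre-treatment baselines for vitamin C and the redox markers. Apply the same rule in both arms. Placebo patients also receive an infusion, so the rule can be applied without unblinding.
- Keep and report the flagged values. Setting them all to missing could discard most baselines if the Interventions timing was followed, including placebo values that contain no vitamin.
- Report between-arm comparisons at the later time points, which do not depend on the first sample.

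The cost is a wording change in two sections, an instruction to the staff who draw the blood, two recorded times per patient and a check of existing records. No extra sample is needed. A pre-dose sample that was missed cannot be recovered, so the change should be made while recruitment continues.
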